### Statistical analyses

The statistical analyses mentioned below will be performed by a bio-statistician not affiliated with our study. Data from CRFs will be computed by two different researchers. Primary results will be based on the intention-to-treat principle. Data for feasibility and safety analysis will be presented as relative frequencies using descriptive statistics. The primary and secondary efficacy outcome measures will use analysis of covariance (ANCOVA) to compare the means between three groups at each time point after adjusting for the fixed factors (gender) and covariates (age, baseline scale score). Multiple comparisons between groups will be performed using the least significant difference (LSD) test. Repeated measures analysis of variance will be performed to determine whether the treatment effects changed over time. The missing values of the efficacy outcome measurements will be managed using the last-observation-carried-forward method. Additionally, sensitivity analysis will be further performed using original data without replacing values missing from the efficacy outcomes.

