## Background

Major depressive disorder (MDD) is a long-lasting mental disturbance [1]. In China, the lifetime prevalence of MDD is approximately 3.3% [2]. It was accidentally observed that patients treated with reserpine, an antihypertension drug that depletes catecholamines, experienced depression, indicating a possible relationship between depletion of norepinephrine or 5-hydroxytryptamine in the brain and affective disorders [3]. Since then, the pharmacology of antidepressants (ADs) has generally been based on the classical monoaminergic hypothesis. To date, the selective serotonin reuptake inhibitors (SSRIs) have generally been selected when treating moderate to severe MDD.

Overall, with adequate first-line pharmacological treatment, 50–75% of patients experience symptom alleviation while the remaining exhibit no response to treatment. Generally, symptom alleviation requires 4–6 weeks after starting medication [4, 5]. Rapid response to treatment could improve patients’ adherence to regular drug intake and strengthen their confidence in overcoming depression, thus largely minimizing the risk of suicide. It may be true that the more progress made in the early treatment phase (first 2 weeks), the more favorable the future outcome that could be achieved [6]. Therefore, researchers anticipate the development of novel fast-acting ADs with minimal side effects.

One major strategy revolves around the modulation of the glutamatergic system. Ketamine, a non-competitive *N*-methyl-D-aspartate (NMDA) receptor antagonist, has attracted considerable attention. However, concern regarding potential drug abuse and psychotomimetic manifestations related to NMDA receptor blockage have prevented its broad clinical administration, particularly in individuals with a history of psychosis [7, 8].

Depression has been considered a syndrome rather than a single disease because even though patients exhibit the same clinical manifestations, the underlying etiology is highly heterogeneous [9]. We intend to identify an AD predominantly based on “the dysfunctional energy homeostasis hypothesis.”.

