### Discontinuation criteria

If participants meet one of the following criteria, the study drugs will be withdrawn:■ The drug-related utilization ratio (number of actual tablets taken/number of planned tablets × 100%) is less than 80% or greater than 120%■ The risks in continuing to participate outweigh the benefits of our study due to the appearance or exacerbation of other diseases■ The aggravation of patients’ mental conditions, such as evolution into severe depression or manic episodes, a high risk of suicide attempts or suicidal acts, which would require altering medical treatment during the study period■ Severe side effects, severe adverse events; and■ Anticipated or accidental pregnancy■ Patients can leave our trial at any time for any reason■ The reason for withdrawing should be recorded on the Case Report Form (CRF)

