### Primary efficacy outcome measures

The reduction rate of the HAMD 24 score both in overall and in each subset item is defined as (Scores of each evaluation time point − baseline scores)/Baseline scores.

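### Carrying the last observation forward as the main missing-data method can bias the week-4 to week-6 efficacy comparison against an arm that loses more patients, or loses them sooner

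*Protocol article*

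**What the plan says.** All of the analysis text is in the Statistical analyses section of the protocol article.

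- Efficacy outcomes are analysed by ANCOVA "to compare the means between three groups at each time point", adjusted for gender, age and the baseline score.
- On the time course: "Repeated measures analysis of variance will be performed to determine whether the treatment effects changed over time".
- On missing data: "The missing values of the efficacy outcome measurements will be managed using the last-observation-carried-forward method".
- As a check, "sensitivity analysis will be further performed using original data without replacing values missing from the efficacy outcomes".
- On the analysis set: "Primary results will be based on the intention-to-treat principle".

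Other sections bear on the point. The Background says: "Generally, symptom alleviation requires 4–6 weeks after starting medication". Interventions gives fluoxetine to every arm for 6 weeks and restricts infusions to the 14 days in hospital; the abstract places the last assessment at week 10. Discontinuation criteria withdraw study drug for severe side effects, for clinical worsening, or when the tablet-use ratio "is less than 80% or greater than 120"%. Sample size assumes drop-out under 15%, with 14 enrolled and at least 12 remaining per arm. The Discussion says efficacy trends will inform whether to run a full-scale trial and how large to make it.

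**The concern.** LOCF assumes that a patient who leaves would have stayed at the last recorded score. The protocol's own expectation contradicts this for early leavers: they go before the response that fluoxetine should bring in every arm, while those who remain go on improving. The filled-in values then enter the analysis as if they had been measured.

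If losses are equal in number and timing and the arms do not truly differ, the error cancels between arms. If one arm loses more patients, or loses the same number sooner, it does not cancel. The flat imputed profiles also enter the group-by-time comparison, which is how the plan judges change over time in a study of a proposed fast-acting effect.

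Unequal loss is plausible on the protocol's own terms. Severe side effects lead to withdrawal of study drug, and the Discussion notes that palpitations could occur if ATP is infused too fast. What is at stake is the efficacy trend that will help decide on, and size, the full trial.

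**Working it through.** **Planned drop-out.** 2/14 = 14.3%, which is under 15% and leaves 12. 3/14 = 21.4%, which is over. So the plan's own figures allow at most 2 losses per arm.

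**Bias formula.** With no true difference between arms and equal timing of exit:

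bias = (difference in number lost ÷ 14) × (later improvement missed).

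The improvement missed is not in the documents. I assume 10 HAMD-24 points and show 5 to 15.

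| Lost (arm A v arm B) | Points missed | Bias against arm A |
|---|---|---|
| 2 v 2 | 10 | 0/14 × 10 = 0 |
| 2 v 1 | 10 | 1/14 × 10 = 0.7 |
| 2 v 0 | 5 | 2/14 × 5 = 0.7 |
| 2 v 0 | 10 | 2/14 × 10 = 1.4 |
| 2 v 0 | 15 | 2/14 × 15 = 2.1 |

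The primary efficacy outcome is change divided by baseline. At an assumed baseline of 28, a bias of 1.43 points is 1.43/28 = 5.1 percentage points.

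**Simulation.** 4,000 runs, 14 per arm. Assumptions, none of them in the documents: HAMD-24 means 28, 24, 20, 15, 12 and 12 at baseline and weeks 1, 2, 4, 6 and 10; SD 4 at baseline and 6 later; correlation 0.6; random drop-out; two-sided 5% level. The week-6 ANCOVA adjusted for baseline only. The group-by-time test used the Greenhouse-Geisser correction.

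Week-6 reduction rate, ATP minus saline, no true effect (positive means ATP looks worse):

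- 2 ATP patients lost after week 1, none elsewhere: +6.3 percentage points with LOCF, 0.1 unimputed. False rejection was 9.7% against 5.2%. The formula agrees: 2/14 × (24 − 12) = 1.71 points, and 1.71/28 = 6.1%.
- 2 lost in every arm, ATP after week 1 and the others after week 4: +4.6 with LOCF, −0.1 unimputed. Earlier timing alone is enough. By formula: 2/14 × (12 − 3) = 1.29 points, and 1.29/28 = 4.6%.
- 2 lost in every arm after week 1: 0.3 with LOCF, 0.4 unimputed, so no bias. LOCF false rejection fell to 0.9%, because the filled-in values add spread.

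With a true 4-point benefit from week 2 (3 points at week 1) and 2 ATP patients lost after week 1, the estimate was −14.6 with full data, −14.7 unimputed and −7.9 with LOCF. Power was 56%, 52% and 14% respectively.

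Group-by-time rejection with no true effect was 6.8% with LOCF against 4.3% with full data when 2 were lost in one arm after week 1. It was 0.6% against 3.9% when 2 were lost after week 1 in every arm.

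**The case against.** The best defence is that the plan already contains the check that would expose the problem. The unimputed analysis gave differences near zero in every no-effect scenario above, and the article puts feasibility and safety first and says the sample cannot show significant efficacy differences. This lowers the stakes but does not remove the point. LOCF still produces the headline efficacy result, the plan does not say which result prevails if the two disagree, and unimputed data did well here partly because drop-out was simulated as random.

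Several stronger readings are tempting, and the documents do not support them:

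- **That drop-out will probably be worse on ATP.** The palpitations remark is conditional on too fast an infusion and is linked to nocebo effects on efficacy, not to leaving the trial. Infusions also stop after 2 weeks.
- **That 3 or 4 of 14 ATP patients might leave.** This exceeds the planned rate, so figures built on it do not describe the plan.
- **That the sensitivity analysis is complete-case.** The text says only that missing values are not replaced. For a per-visit ANCOVA this most naturally means everyone seen at that visit. Loss of patients with any missed visit is a property of classical repeated-measures ANOVA, not something the article states.
- **That the bias runs the same way at week 10.** Trial fluoxetine ends at week 6. If scores then worsen, LOCF could favour the arm that lost patients between weeks 6 and 10.
- **That withdrawn patients are no longer assessed.** The article says study drug is withdrawn and does not say assessments stop. It is a condensed account, and its timeline figure is not available here.
- **That the full trial's standard deviation will be wrong.** The article does not say that the LOCF standard deviation will be the one carried forward.

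**Conclusion.** The point holds as a defect in a stated method, and it should be changed. As the main analysis, LOCF conflicts with the protocol's own expected time to response. It can shift the week-4 to week-6 comparison against an arm with more or earlier losses. Within planned drop-out the shift is 0.7 to 1.4 HAMD-24 points if 10 points of improvement are missed, and 0.7 to 2.1 points for 2 against 0 over the range of 5 to 15 points missed. It is zero with equal numbers, equal timing and no true effect.

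The size rests on assumed trajectories and visit times. The direction rests on scores still improving after exit, which fits the 4–6 week expectation up to week 6 but not necessarily at week 10. Distortion of the group-by-time test is modest at planned drop-out: mild inflation if one arm alone loses patients, and conservatism if all arms lose them early.

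**What to change.** Make a mixed model for repeated measures on observed data the main efficacy analysis, replacing both the LOCF-based ANCOVA and the repeated-measures ANOVA. Specify arm, visit and arm × visit, with baseline score, age and gender; an unstructured covariance, with a prespecified simpler structure such as AR(1) or compound symmetry if it does not converge; and Kenward-Roger degrees of freedom. The model gives the between-arm contrast at each visit and the test of change over time, and it uses a leaver's earlier post-baseline scores. Keep LOCF as a sensitivity analysis only. The discontinuation criteria need no change for this.

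The cost is about a paragraph of wording. The downside is that the model assumes data missing at random, which may fail if patients leave for reasons their recorded scores do not capture. With 42 patients it may also have to use the simpler covariance.

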### Harms

After initiating treatment, the participants will be encouraged to report any discomfort, and the physicians will record it on CRF and determine whether the discomfort is related to the study drugs. If any adverse events occurred, they will be documented on AER forms and entered into CRF, including the nature of the events, onset dates, causality with the study drugs, final diagnoses, severity, any given corrective managements, and clinical outcomes. Furthermore, physicians will provide expert care until the patients recover, the relevant expenses will be covered and financial compensation will be provided to patients through study funding. Severe adverse events will be reported to the hospital Ethics Committee, PI and sponsor within 24 h, and they will decide whether the study procedures should continue or cease based on the patients’ best interests.

### Ethics and dissemination

#### Research Ethics approval

The trial protocol and informed consent form adhere to the principles of the Declaration of Helsinki [44], and template advertisements were reviewed and approved by the Medical Ethics Committee of Zhujiang Hospital of South Medical University prior to the start of our study on 28 April 2017 (Ethics Reference Number: 2017-SJNK-001).

#### Protocol amendments

Any modifications to the protocol referring to the conduct of the study or potential benefits to the patient or that could affect patient safety should be reapproved by the Medical Ethics Committee and sponsor prior to implementation.

#### Consent or assent

To those who meet the requirements, a consent form will be offered, covering the study name, registered information, inclusion/exclusion criteria, treatment plan and obligations, possible drug-related side effects, and expenses during participation, and a further period will be provided for the patients to consider whether they will participate. Any doubts can be discussed and allayed before participation, ensuring unambiguous comprehension of our study. Participants will retain a copy signed by both parties.

#### Confidentiality

Participants’ study-related information, including personal identification data, medical history, and collected assessment materials, will be stored in a locked file cabinet at the study site, to which only assigned study researchers can be permitted access for data collection or analysis. The privacy of the participants will be guaranteed by the PI. Documents submitted to DMC, Zhujiang Hospital, Southern Medical University, will be identified by the allocated ID only. Additionally, electronic data records for statistical purposes will be secured with a password-protected access system.

#### Access to data

The PIs will have full access to the complete trial data, all of which can be retrieved for later verification and validation. Moreover, no trial-related documents will be destroyed without prior joint permission from the PI and sponsor.

#### Ancillary and post-trial care

Following the study timeline, at the final visit during our study period, the physician will recommend a post-trial treatment plan based on the patient’s current condition and will prescribe drugs with the patient’s consent.

#### Dissemination policy

Our research has been registered at ClinicalTrials.gov with the assigned ID of NCT03138681. All publications and representations related to our study should be authorized by the PI in advance. Full access to the detailed protocol and database of our study information can be discussed with the PI. After study completion, final results are expected to be published and presented at related conferences.

## Discussion

Multiple studies have revealed altered energy metabolism in brain regions. With the utilization of in-vivo phosphorous magnetic resonance spectroscopy, nucleoside triphosphate (NTP), which mainly derives from ATP, has shown to be decreased in depressed subjects [45]. Meanwhile, in MDD patients treated with either SSRI sertraline, or creatine, or thyroid hormones, which have been shown to increase brain bio-energetic metabolism, NTP levels are significantly increased in treatment responders compared with non-responders [26, 46, 47]. Compared with conventional ADs, novel compounds with fast-acting AD effects will minimize the time lag to obtain treatment results, enhance patients’ adherence, reduce the suicide rate and aid psychosocial recovery.

Our preclinical studies showed that ATP, as well as PCr, displayed rapid AD effects in animal models of depression. To our knowledge, our study is the first clinical attempt to add ATP/PCr intravenously with the orally administered fluoxetine to patients with moderate to severe MDD.

PCr, after being diluted in 0.9% saline 100 ml, should be infuse intravenously within the next 40 min. As this is a double-blinded experiment, both ATP and placebo group should be administered in less than 40 min. However, if the infusion rate of ATP is too fast, some patients might experience palpitations. We assume that the nocebo effects might influence the efficacy results in ATP group.

After enrollment, patients will be hospitalized for the initial 14 days, enabling early detection, screening and treatment for adverse events when they occur, minimizing patient concern about the therapy, and enhancing drug adherence. Enrolled patients will be registered as a regular hospitalized patient, and be put in a regular two-/three-bed ward. The interaction influences among patients sharing the same ward will be evaluated through a questionnaire received in last visit of study period. However, compared with those suffering from physical diseases, most patients with mental illnesses including MDD are reluctant to be hospitalized, which adds to the recruitment difficulties. Negative family interactions, and social milieu could be unfavorable for recovery from depression [48]. Hospitalization removes patients from a real-world setting. Therefore, the isolation of passive psychosocial influences or, instead, safe surroundings and clinical care, might exert beneficial effects on MDD patients. However, those with welcoming, supportive supervised housing may return home after day treatment. The tailored hospitalization setting, whether they stay in the ward for the full day or only during the daytime, is performed according to the specific characteristics of the enrolled subjects’ both personality and environmental factors for the purpose of providing a patient-centered treatment setting [49]. We will examine the impact of this setting and discuss in the final report.

The small sample size of this pilot study does not allow us to observe significant statistical differences of efficacy outcomes among groups. However, existing trends of efficacy as well as the feasibility assessment will help determine whether to conduct a powered, full-scale trial and help appropriate sample size calculation.

### Trial status

Recruitment of participants is currently ongoing.

## Abbreviations

ADs: Antidepressants
AER: Adverse events report
ANCOVA: Analysis of covariance
ATP: Adenosine triphosphate
CGI: Clinical Global Impression
CK: Creatine kinase
CoQ10: Coenzyme Q10
CRF: Case Report Form
DMC: Data Monitoring Committee
ECG: Electrocardiogram
EEG: Electroencephalogram
HAMD: Hamilton Depression Rating Scale
IV: Intravenous
LSD: Least significant difference
MDD: Major depressive disorder
NMDA: *N*-methyl-D-aspartate
NTP: Nucleoside triphosphate
OXPHOS: Oxidative phosphorylation
PCr: Phosphocreatine
PFC: Prefrontal cortex
PHQ-9: Patient Health Questionaire-9 items
PIs: Principle investigators
SAS: Statistical Analysis Software
SERS: Side Effects Rating Scale
SFDA: State Food and Drug Administration
SSRIs: Selective serotonin reuptake inhibitors
